## Methods

### Study Design

The PICMOA-2 trial is an open-label, 6-month RCT with 2 parallel groups, including 1 intervention group and 1 passive control group. The overall timeline of the procedure is shown as a SPIRIT flow in Table 1. The main and secondary outcomes will be assessed at baseline and after a 6-month intervention period.

**Table 1 table1:** Overall timeline of the procedure of the PICMOA-2 trial.

Time point				Enrollment		Allocation		Post allocation			Evaluation
				–t_1_		0		t_1_	t_2_		t_3_

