### Sample Size

We used G*power [38] to calculate the sample size, assuming the following conditions: 2-sided hypothesis test; medium effect size (f=0.25); 95% power; an analysis of variance model between groups over time; and 5% α level. Therefore, 65 participants are required, with a 20% dropout rate.

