### Statistical Analysis

This study evaluates the effects of the PICMOA-2 intervention on outcome measurements. Linear mixed models with random intercepts for outcome measurements will be used to estimate the intervention effects. Our model will include the group assignment factor, time factor, and group × time interaction term and evaluate the intervention effect from the interaction term. As a secondary aim, we will test whether the intervention effects varied with the covariates at baseline to examine the effective target attributes.

All analyses will be conducted using the R software (The R Foundation). Statistical significance will be set at *P*<.05.

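### The planned group × time estimate is valid but less precise than one that adjusts for the baseline score, by an amount that depends on an unstated correlation

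*Protocol article*

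**What the plan says.** The Statistical Analysis section of the protocol article names the model: "Linear mixed models with random intercepts for outcome measurements will be used to estimate the intervention effects". Its fixed effects are the "group assignment factor, time factor, and group × time interaction term", and the plan is to "evaluate the intervention effect from the interaction term". No adjustment for the baseline value of the outcome is named. Baseline covariates enter only for the secondary question of effect modification.

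The Study Design section fixes two measurement times: "The main and secondary outcomes will be assessed at baseline and after a 6-month intervention period". Table 1 places the baseline outcome tests at the enrolment time point, before allocation.

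The Sample Size section uses a matching model, "an analysis of variance model between groups over time", with a "2-sided hypothesis test" and a "medium effect size (f=0.25"). It gives no correlation between baseline and follow-up.

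**The concern.** With one baseline and one follow-up, a free group term makes the model estimate a baseline difference whose true value is zero by design. The interaction then subtracts the whole observed baseline difference from the 6-month difference. A more precise estimate subtracts only the part that baseline predicts.

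Precision is at stake. Recruitment closed at 66 participants, and the Limitations section says the sample size was set as a minimum for feasibility. The choice of analysis is therefore the main remaining way to gain precision without collecting more data.

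**Working it through.** **Inputs.** From the protocol: two arms, 1:1 allocation, two visits, two-sided 5% level, 95% power, f = 0.25, 20% dropout, 65 required, 66 randomised. Assumed: rho (range shown), equal variance at both visits (SD = 1), equal arms.

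**1. The protocol's own figure.** For a repeated-measures ANOVA interaction with m = 2 visits, lambda = f² × N × m / (1 − rho), with 1 and N − 2 degrees of freedom. At rho = 0.5 and N = 54, lambda = 0.0625 × 54 × 2 / 0.5 = 13.5 and power is 0.950. Then 54 × 1.2 = 64.8, which rounds up to the stated 65. Rho = 0.3 needs 76 and rho = 0.6 needs 44 before dropout, so 0.5 is the value that fits, although the article does not state it. With two groups and two visits, f = 0.25 is a difference in change of 4 × 0.25 = 1.0 SD of a single measurement.

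**2. What the planned model estimates.** In simulated complete data (N = 66, 100 data sets per scenario), the interaction equalled the difference in mean change to about 1e-15. The standard errors agreed to about 1e-7.

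**3. Variances.**
- Planned interaction: 2(1 − rho) × 4/N
- Baseline-adjusted: (1 − rho²) × 4/N
- Ratio: (1 + rho)/2

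ANCOVA carries a further small-sample factor of 1 + 1/(N − 4). At N = 66, in SD units:

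| rho | SE planned | SE adjusted | SE ANCOVA with factor | SE ratio (with factor) |
|---|---|---|---|---|
| 0.3 | 0.291 | 0.235 | 0.237 | 0.806 (0.813) |
| 0.5 | 0.246 | 0.213 | 0.215 | 0.866 (0.873) |
| 0.7 | 0.191 | 0.176 | 0.177 | 0.922 (0.929) |
| 0.8 | 0.156 | 0.148 | 0.149 | 0.949 (0.956) |
| 0.9 | 0.110 | 0.107 | 0.108 | 0.975 (0.983) |
| 0.95 | 0.078 | 0.077 | 0.078 | 0.987 (0.995) |

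Comparing the 6-month scores alone, with no use of baseline, has SE √(4/66) = 0.246. At rho = 0.5 the planned estimate does no better than that.

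**4. Power with 52 completers (65 × 0.8), ANCOVA factor included.** The 0.5 SD effect is an assumption, not a protocol figure.
- rho 0.5: SE 0.277 to 0.243, power 42% to 52%
- rho 0.7: SE 0.215 to 0.200, power 63% to 69%
- rho 0.8: SE 0.175 to 0.168, power 80% to 83%

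At the protocol's implied 1.0 SD, rho 0.5 and 54 completers, power goes from 95.0% to 98.5%.

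**5. Dropout.** With 20% random loss from 66, the mixed model also uses participants who have only a baseline score, so it is no longer identical to a completers' change score. Mean SE, planned against baseline-constrained, was 0.268 against 0.239 at rho 0.5 (ratio 0.89) and 0.209 against 0.196 at rho 0.7 (ratio 0.94). The gain is slightly smaller but remains.

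**6. Unequal variances.** As an illustration, take rho 0.6 and a follow-up SD 1.4 times the baseline SD. The change-score variance is 1 + 1.96 − 2 × 0.6 × 1.4 = 1.28. The ANCOVA variance is 1.96 × (1 − 0.36) = 1.254, a gain of only 2%. In simulation, dropping the group term while keeping only a random intercept reported an SE of 0.244 against a true 0.282. ANCOVA stayed calibrated (0.277 against 0.274).

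**The case against.** The strongest defence is that nothing in the plan is invalid. The interaction is unbiased under randomisation, its standard error already allows for chance baseline imbalance, and the sample size was calculated for the same type of analysis. On the protocol's own effect size, the planned analysis reaches its 95% target. All of this stands. A reader might infer that the planned estimate is biased by baseline imbalance or regression to the mean. The documents do not support that: the outcomes are measured before allocation, so averaged over randomisation there is no bias.

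The defence also says that the gain depends on a correlation the article does not give, and on equal variances. That stands too, and it is why a range is shown. Quoting only the rho 0.5 result would overstate what can be promised.

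Finally, there is a prespecification cost. The post-intervention evaluation was scheduled for March 2024 and the article appeared in July 2024, so changing the published primary model in an open-label trial needs care. This bears on how the change is made. It does not alter the comparison of precision.

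**Conclusion.** The point holds as one of efficiency, not validity. For complete pairs, the planned model is a change-score analysis, and adjusting for a baseline score that is already collected is expected to be more precise. Under equal variances, the reduction in standard error runs from about 13% at rho 0.5 to 4-5% at rho 0.8 and close to nothing above 0.95. Dropout trims it slightly, and unequal variances can shrink it further. The ordering is an expectation over repeated trials, and a single data set may differ a little. The gain is worth taking in a trial of 66 people, but the figures do not show that the planned analysis fails or that the trial misses its own power target because of it.

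**What to change.** For verbal fluency and every continuous secondary outcome, estimate the effect in one of two ways:
- ANCOVA: regress the 6-month score on arm and baseline score.
- A baseline-constrained longitudinal model: time and group × time, no group main effect, with an unstructured covariance over the two visits.

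Deleting the group term from the random-intercept model is not an adequate substitute, because that model forces equal variances and can report too small a standard error. The stratification factors (sex and MMSE stratum) can be added to either option. Keep the published interaction model as a sensitivity analysis.

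This needs a sentence in the analysis plan and a small change in the R code, with no new data. The downside is a departure from the published primary model. It should be dated, justified on precision alone, and made before unblinded outcome data are analysed.

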**Conclusions:**

This protocol outlines the randomized controlled trial study design evaluating the effect of a 6-month intervention with PICMOA-2. This study will provide evidence on the effectiveness of social interventions on cognitive function and identify effective target images for remote social intervention.

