#### Covariates

The covariates from the questionnaire include the following variables to describe participants’ demographics: age, sex, educational attainment, social isolation (the Lubben Social Network Scale-6) [37], and familiarity with devices such as smartphones, PCs, and email. Blood samples are also collected, with the measurement of blood-based biomarkers, including plasma neurofilament light chain (NfL), plasma tau, and tau in neuron-derived extracellular vesicles from plasma, which may reflect neuronal condition.

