### Randomization and Blinding

Stratified block randomization, a block design (2, 4, and 6 block sizes) with a 1:1 allocation, was performed using the University Hospital Medical Information Network Internet Data and Information System for Clinical and Epidemiological Research Cloud version [39]. The participants were allocated to either the intervention or the control group. Sex (male or female) and MMSE scores (28 or higher and 27 or lower) at baseline were used for stratification. [name] is responsible for the randomization. As this study uses an open-label design, we aim to prevent potential assessment bias by blinding the assessors.

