## Results

Recruitment began in April 2023 and ended in July 2023. In total, 66 participants were enrolled and randomly allocated to intervention or control groups. As of January 1, 2024, the intervention is ongoing. Participants are expected to complete the intervention at the end of February 2024; the postintervention evaluation will be conducted in March 2024.

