## Discussion

### Findings and Strength

This protocol aimed to evaluate the effect of a 6-month PICMOA-2 intervention, a web-based group conversational intervention, on cognitive function, frailty, and social and psychological indicators to determine the effectiveness of a web-based remote conversational intervention that we originally developed.

This study has several strengths. First, it may have clinical significance by accumulating evidence on the effectiveness of social interventions on cognitive function and digital health practices. Although large-scale observational studies have demonstrated a link between social interaction and cognitive health [2-7], whether social interventions can slow cognitive decline remains unknown. Since there is low evidence of social intervention and there are no clear clinical guidelines, this study may add knowledge on the effectiveness of social intervention. Second, this study examined whether there are differences in intervention effects depending on attributes by collecting subjective and laboratory data. A previous study in a completed clinical trial on mild Alzheimer disease suggested that baseline plasma NfL, which is a neurological biomarker, holds independent information on short-term cognitive decline [40]. Our previous RCT of a face-to-face conversational intervention program also found a positive intervention effect in the group with lower levels of NfL [23]. In addition, our previous PICMOA trial using smartphones suggested that familiarity with digital devices causes differences in the intervention effect [27]. This research may contribute to the search for clues to effective target images for remote social intervention by examining effective targets. Finally, this study directly recruited community-dwelling older adults mainly via mail in cooperation with the municipal government. This method can eliminate selection bias and enhance generalizability to real community intervention settings compared with recruiting from specific organizations or surveys.

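### Unadjusted tests of at least eight baseline modifiers in 66 people cannot support the stated promise to identify who benefits; a target found has a high risk of being chance or exaggerated

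*Protocol article*

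**What the plan says.** The Statistical Analysis section of the protocol article sets the main analysis as a linear mixed model judged by its group-by-time term. It then adds, as a secondary aim, that "we will test whether the intervention effects varied with the covariates at baseline to examine the effective target attributes". It does not rank the covariates. One threshold follows for everything: "Statistical significance will be set at" P<.05.

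The Covariates section gives two sets:
- from the questionnaire: "age, sex, educational attainment, social isolation (the Lubben Social Network Scale-6) [37], and familiarity with devices such as smartphones, PCs, and email";
- from blood: "plasma neurofilament light chain (NfL), plasma tau, and tau in neuron-derived extracellular vesicles from plasma".

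The Sample Size section covers only a group-over-time analysis of variance. The Results section reports that "66 participants were enrolled and randomly allocated to intervention or control groups".

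The article describes the aim at two strengths. The Conclusions of the abstract and of the Discussion both say the study will "identify effective target images for remote social intervention". The Findings and Strength section says only that the work may help in looking for clues. That section also gives prior reasons for two modifiers. One is NfL: "Our previous RCT of a face-to-face conversational intervention program also found a positive intervention effect in the group with lower levels of NfL". The other is familiarity with digital devices, from the earlier smartphone trial, which the Introduction also describes.

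**The concern.** A set of at least eight unranked modifier tests at a flat 5%, in a trial sized for something else, has two weaknesses. It can produce a target when none exists, and it has little chance of detecting a real modifier of moderate size. When it does detect one, the estimate will tend to be too large.

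What is at stake is the conclusion about whom to offer the program to. The two questions this trial is well placed to ask, whether the NfL and device-familiarity findings replicate, get no more weight in the analysis than the other covariates.

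**Working it through.** **Inputs from the protocol article**
- Covariates: age, sex, education, LSNS-6 and device familiarity (5), plus NfL, plasma tau and vesicle tau (3), so 8. Device familiarity counts once, as in Table 1. The blood list is introduced as a partial one, so 8 is a minimum.
- Threshold: 5%, two-sided (Statistical Analysis; Sample Size).
- Randomized: 66, 1:1 (Results; Randomization and Blinding). With the planned 20% dropout, 66 × 0.8 = 52.8, about 53.
- Sizing: f = 0.25, 95% power, two measurement times, stated N = 65.

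**Assumptions, not in the article**
- Within-person correlation 0.5.
- A modifier that splits the sample in half.
- Independent tests.
- Effects that differ between the halves by 0.5 or 1.0 SD of change.

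**1. The plan's own figure.** For the group-by-time test, λ = f² × N × m / (1 − ρ) = 0.0625 × N × 2 / 0.5 = 0.25N. Power reaches 95.0% at N = 54, and 54 × 1.2 = 64.8, so 65 is reproduced. It covers the group-over-time effect and nothing else. For two arms compared on change, λ = N × d² / 4, so d² / 4 = 0.25 and d = 1.0. Under the assumed correlation, the trial is sized for a group difference of 1.0 SD of change.

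**2. False targets if no modifier is real**
- Eight tests on one fluency score: 1 − 0.95^8 = 0.337, about 34%.
- Expected false positives: 8 × 0.05 = 0.4 per score, whatever the correlation.
- Positive correlation between tests lowers the 34% but not the 0.4.

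**3. Power for a real modifier.** With four equal cells, the standard error of the difference in effect is 4 / √N in SD of change: 4 / √66 = 0.492 and 4 / √53 = 0.549. From the noncentral t with N − 4 degrees of freedom:

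| True difference in effect | N = 66 | N = 53 |
|---|---|---|
| 0.5 SD | 17.0% | 14.5% |
| 1.0 SD | 51.6% | 43.0% |

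So a modifier as large as the main effect the trial was sized for is found about half the time.

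**4. Exaggeration.** At N = 66 the critical t is 2.00, so significance needs an estimate of at least 2.00 × 0.492 = 0.98 SD. A true 0.5 SD modifier must be overstated by 0.98 / 0.5, about twofold, to reach P<.05 in its true direction.

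**5. Share of significant modifiers that are false.** With K tested and r real, the share is 0.05(K − r) / [0.05(K − r) + power × r]. For K = 8:

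| Real modifiers | 0.5 SD, N = 66 / 53 | 1.0 SD, N = 66 / 53 |
|---|---|---|
| 1 | 67% / 71% | 40% / 45% |
| 2 | 47% / 51% | 23% / 26% |

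**6. Effect of restricting the tests**
- Two modifiers at 0.025 each: 1 − 0.975² = 4.9% chance of a false target on one score, against 34%. Power falls to 11% (N = 66) or 9% (N = 53) for 0.5 SD, and to 40% or 32% for 1.0 SD.
- Bonferroni over all eight (0.05 / 8 = 0.00625): at N = 66, power is about 4% for 0.5 SD and 22% for 1.0 SD. Adjustment alone does not make the open search workable.

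**The case against.** **A fuller plan may settle this.** A condensed article may leave the list of modifiers, their order and any adjustment to an analysis plan that is not shown. This is fair: testing every covariate is a reading of the text, not its wording. But an unseen plan cannot raise power at 66 people, and it does not alter the published statement that targets will be identified.

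**The article already hedges.** The Introduction calls this a secondary objective, Findings and Strength speaks of clues, and Limitations concedes a feasibility-driven sample and asks for large-scale validation. These hedges are real and should be credited. However, the call for validation concerns whether the intervention works, not who benefits. The Conclusions that follow it return to the stronger claim.

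**The two prior hypotheses are visible.** Findings and Strength singles out NfL and device familiarity, so a reader can see which modifiers have support. That stands, and a result on either would be more credible than one on the other covariates. The analysis section still gives them no priority.

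**The power figures are conditional.** The 0.5 and 1.0 SD differences and the half-and-half split are assumptions, and several covariates are continuous. That also stands, so a range is shown.

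**Two stronger readings are tempting.** A reader might infer that any target found is more likely chance than real. The article does not support that: in the cases in step 5 the false share runs from 23% to 71%, depending on how many modifiers are real and how strong they are. A reader might also count smartphone, PC and email familiarity separately, giving ten tests and 1 − 0.95^10 = 40%. Table 1 lists one familiarity variable, so eight is the supported count.

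**Conclusion.** The concern holds in a limited form. As written, the secondary analysis carries about a 34% chance of at least one false target per fluency score if nothing is real (eight independent tests; less if they are correlated). Power is 14% to 17% for a 0.5 SD and 43% to 52% for a 1.0 SD difference in effect, under a balanced binary modifier. A 0.5 SD modifier that reaches significance in its true direction at N = 66 is overstated about twofold; this last result does not depend on how many modifiers are real.

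A target found therefore has a high risk of being chance or exaggerated, though not necessarily a better-than-even chance of being false. The design supports the modest aim in Findings and Strength, not the promise in the two Conclusions.

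**What to change.** Before any unblinded analysis, and with a dated record:

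1. Name NfL and device familiarity as the two prespecified modifiers. Test each on the primary fluency outcome, with 5% shared between them (0.025 each if one fluency score is used; 0.05 / 4 = 0.0125 each if phonemic and semantic fluency are both tested).
2. Confirm that the blood sample precedes the first intervention session. Table 1 places it at t1, after allocation and at the same time point as the equipment practice and test session, so its status as a baseline value needs to be stated.
3. Report all other covariates as exploratory interaction estimates with confidence intervals and no claim of significance.
4. In both Conclusions, and in the results report, replace the promise to identify targets with a statement that the study will test whether two previously suggested modifiers replicate and will explore others. Because the article is published, this means a correction or note there and the right wording in the results paper.

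**Cost.** Only wording and documentation change; no new data are needed. Post-intervention assessment was due in March 2024 and the article is dated July 2024, so the change is credible only if it is recorded before group-level results are seen. The other covariates lose confirmatory status and the stated conclusion becomes more modest. Power stays low and drops further with the shared 5%: from 14–17% to 9–11% for 0.5 SD, and from 43–52% to 32–40% for 1.0 SD. A null result on either modifier would therefore not rule it out.

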### Ethical Considerations

This trial was approved by the Ethics Committee of RIKEN (RIKEN-W1-2022-063) and was registered in the University Hospital Medical Information Network clinical trial registry (UMIN000050877).

## Results

Recruitment began in April 2023 and ended in July 2023. In total, 66 participants were enrolled and randomly allocated to intervention or control groups. As of January 1, 2024, the intervention is ongoing. Participants are expected to complete the intervention at the end of February 2024; the postintervention evaluation will be conducted in March 2024.

## Discussion

### Findings and Strength

This protocol aimed to evaluate the effect of a 6-month PICMOA-2 intervention, a web-based group conversational intervention, on cognitive function, frailty, and social and psychological indicators to determine the effectiveness of a web-based remote conversational intervention that we originally developed.

This study has several strengths. First, it may have clinical significance by accumulating evidence on the effectiveness of social interventions on cognitive function and digital health practices. Although large-scale observational studies have demonstrated a link between social interaction and cognitive health [2-7], whether social interventions can slow cognitive decline remains unknown. Since there is low evidence of social intervention and there are no clear clinical guidelines, this study may add knowledge on the effectiveness of social intervention. Second, this study examined whether there are differences in intervention effects depending on attributes by collecting subjective and laboratory data. A previous study in a completed clinical trial on mild Alzheimer disease suggested that baseline plasma NfL, which is a neurological biomarker, holds independent information on short-term cognitive decline [40]. Our previous RCT of a face-to-face conversational intervention program also found a positive intervention effect in the group with lower levels of NfL [23]. In addition, our previous PICMOA trial using smartphones suggested that familiarity with digital devices causes differences in the intervention effect [27]. This research may contribute to the search for clues to effective target images for remote social intervention by examining effective targets. Finally, this study directly recruited community-dwelling older adults mainly via mail in cooperation with the municipal government. This method can eliminate selection bias and enhance generalizability to real community intervention settings compared with recruiting from specific organizations or surveys.

